### Study procedures

Apart from the G8 that is performed to stratify patients between monotherapy and doublet therapy, participants will also undergo a GA. The results from the GA will be used to characterise the study population and find predictors of poor outcomes. The GA will comprise the EuroQol-5D (EQ-5D)^19^ and European Organisation for Research and Treatment of Cancer (EORTC) Core QLQ-C30 questionnaires for QoL, the Katz Activities of Daily Living (ADL),^20^ Lawton Instrumental ADL (IADL)^21^ and home and informal care for physical functioning, the Modified Telephone Interview for Cognitive Status for cognition,^22^ Mini Nutritional Assessment for malnutrition^23^ and Patient Health Questionnaire-2 for mood^24^ (table 1). The GA will be conducted via telephone calls to increase feasibility. Performing a telephone-based GA has proven to be feasible in previous studies with older adults.^25 26^ Comorbidity (assessed with the Charlson Comorbidity Index^27^) and polypharmacy (at least five different types of medication) will be obtained from the medical charts. If the GA identifies geriatric deficits, the treating oncologist will be informed and GA-based interventions will be at their discretion.

**Table 1 T1:** Overview of study procedures

	Screening (T<0)	Prerandomisation	Randomisation (T=0)	Before and after every cycle, until progression	Each 8–12 weeks	After 1 month	After 3 months	After 6 months	After 9 months	After 12 months	End of study
Informed consent		E									
Geriatric-8		E									
Inclusion/exclusion	X										
Patient/tumour characteristics	X										
Laboratory analysis*	X			X							
Toxicity				X							
Radiologic evaluation†	X				X						
Dose reductions				X							
Cycles, n				X							
Hospitalisations				X							
Survival					X						X
EQ-5D‡		E				E	E	E	E	E	
EORTC Core QLQ-C30‡		E				E	E	E	E	E	
Katz ADL‡		E				E	E	E	E	E	
Lawton IADL‡		E				E	E	E	E	E	
Home and informal care‡		E				E	E	E	E	E	
MNA		E									
TICS-M		E									
PHQ-2		E									

Window for questionnaires: ±4 weeks.

X=procedures are standard of care. E=extra procedure in study context.

* Laboratory analyses should at least include total blood count, kidney and liver function.

† Radiologic evaluation: performed according to local standard practice (CT scan, positron emission tomography (PET) scan and/or MRI scan).

‡ Follow-up questionnaires will be performed until disease progression or until 12 months after randomisation in case of no disease progression.

ADLactivities of daily livingEORTCEuropean Organisation for Research and Treatment of CancerEQ-5DEuroQol-5DIADLInstrumental Activities of Daily LivingMNAMini Nutritional AssessmentNnumberPHQ-2Patient Health Questionnaire-2TICS-MModified Telephone Interview for Cognitive Status

After 1 3, 6, 9 and 12 months, alive patients will be invited to complete four short questionnaires on QoL (EORTC QLQ-C30 and EQ-5D) and physical functioning (Lawton IADL and Katz ADL) plus questions about home and informal care. These questionnaires can be answered by telephone or sent by email (whatever the patient prefers) to optimise follow-up data.

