### Treatment monitoring

After each treatment cycle, treatment tolerability (chemotherapy-related toxicity according to the Common Terminology Criteria for Adverse Events (CTCAE) V.5.0^18^) will be assessed. Patients in the upfront dose-reduced arm who have tolerated the first two cycles of their treatment well (no occurrence of grade 2–5 toxicity), can (but do not have to) receive dose-escalation to 100% at the discretion of the treating oncologist and after consultation with the patient. In both arms, toxicity may allow for further dose reductions: if patients experience either grade 3–4 toxicity or unacceptable grade 1–2 toxicity that influences QoL, the oncologist can reduce the dose by 25%. The minimal dose is 50% of full dose: if further (unacceptable) toxicity occurs, the treatment should be discontinued. For neuropathy, in case of grade 2 toxicity, oxaliplatin dose is reduced with 25%. In case of grade 3 neuropathy, oxaliplatin is definitively stopped. After 18 weeks of doublet chemotherapy, maintenance therapy with capecitabine or 5-FU (with or without bevacizumab) can be started at the discretion of the treating oncologist. Chemotherapy treatment will be continued until progression, unacceptable toxicity or a patients’ or clinicians’ decision to stop. If patients develop progression or discontinue first-line treatment due to other reasons (such as toxicity), the study will end and any further treatment lines are allowed by the discretion of the oncologist.

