### Outcome measures

The *primary outcome* of the study is PFS, defined as time from randomisation until either radiological or clinical progression or death due to any cause, whichever occurs first. Timepoints of measurements are presented in table 1. In case of clinical progression as judged by the local principal investigator, local investigators should explain the base of clinical progression. *Secondary endpoints* include QoL (measured by the EQ-5D and EORTC Core QLQ-C30 questionnaires after 1, 3, 6, 9 and 12 months), physical functioning (measured with the Katz ADL, the Lawton IADL and home and informal care after 1, 3, 6, 9 and 12 months), grade≥3 chemotherapy-related toxicity according to the CTCAE during study treatment, dose reductions during study treatment, number of treatment cycles, unplanned hospital admissions within the first year, OS, cumulative received dose and cost-effectiveness in the first year. Predictive geriatric markers of poor outcomes will be identified using the baseline GA.

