#### Secondary outcomes

A logistic regression model will be estimated to study the effect of groups on chemotherapy-related toxicity; the same covariates as discussed before will be included. Due to the presence of repeated measures for QoL and physical functioning, mixed models to investigate the relation between the outcomes and arms will be used. An interaction term between time and arms will be added to the model to quantify the effect of time. The cumulative dose received by patients in each arm (divided by BSA) will be reported, and means will be compared using the t-test. Finally, we will investigate which geriatric domains (assessed by the GA) are associated with toxicity, QoL and physical functioning.

For cost-effectiveness, a cost-utility analysis will be performed (‘costs per quality-adjusted life year (QALY)’) from a societal perspective and with a life-long time horizon, in accordance with the Dutch guidelines for economic evaluations in healthcare.^30^ Costs will include the chemotherapy and other hospital costs (assessed from study registrations) and home and informal care (assessed using patient questionnaires at 1, 3, 6, 9 and 12 months). No impact on productivity costs will be assumed, because of the patients’ age. QALYs will be calculated using the Dutch tariff for the five-level EQ-5D questionnaires filled out by patients.^19^ Mathematical modelling will be used to extrapolate outcomes to a life-time horizon. In the analysis, incremental costs and QALYs will be compared using net-benefit analysis, according to intention to treat.^31^

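### Table 1 ends questionnaires and admission recording at progression, while the text and endpoint definitions run to 12 months; these follow-up rules conflict and must be reconciled

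*Protocol article*

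**What the plan says.** **Questionnaires.** The Table 1 footnote (Study procedures) covers EQ-5D, QLQ-C30, Katz ADL, Lawton IADL and home and informal care: "Follow-up questionnaires will be performed until disease progression or until 12 months after randomisation in case of no disease progression". The paragraph after the table sets visits at 1, 3, 6, 9 and 12 months and says "alive patients will be invited to complete four short questionnaires on QoL" and physical functioning, plus care questions. Being alive is the only condition. Outcome measures defines the endpoint as "QoL (measured by the EQ-5D and EORTC Core QLQ-C30 questionnaires after 1, 3, 6, 9 and 12 months", again with no progression limit, and uses the same time points for physical functioning.

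**Admissions.** The Hospitalisations row of Table 1 is marked in one column only, headed "Before and after every cycle, until progression". Outcome measures lists "unplanned hospital admissions within the first year, OS, cumulative received dose and cost-effectiveness in the first year".

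**End of study.** Treatment monitoring says: "If patients develop progression or discontinue first-line treatment due to other reasons (such as toxicity), the study will end". It does not say whether this means study treatment or data collection.

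**Economic analysis.** Secondary outcomes states that "QALYs will be calculated using the Dutch tariff for the five-level EQ-5D questionnaires filled out by patients". Home and informal care costs come from the same questionnaires to month 12. The comparison is by intention to treat, "from a societal perspective and with a life-long time horizon", with modelling beyond the observed data.

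**The concern.** A site cannot follow both rules. One tells it to stop the questionnaires when the patient progresses; the other tells it to continue while the patient lives. The admissions schedule and the admissions endpoint disagree in the same way. The end-of-study sentence makes the restrictive reading plausible. Taken literally, it goes further and also ends follow-up for patients who stop first-line treatment because of toxicity, a group central to the trial's hypothesis.

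The choice matters because progression is a component of the primary outcome. Stopping there ties the amount of quality-of-life, function, admission and care data to PFS, and PFS may differ between arms. Study objectives expects fewer admissions and lower healthcare costs with dose reduction. If dose reduction shortened PFS, earlier stopping would lower recorded admissions and costs in that arm and so favour the hypothesis. Data never collected cannot be restored by an analysis plan, so this cannot be left to a later document. The article's box of strengths and limitations names quality of life, physical functioning and hospitalisations as a strength of the trial.

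**Working it through.** **Inputs** (Statistics: sample size and power calculations): median PFS 8 months; reference hazard 0.12 per period; accrual 36 and total duration 48 periods; margin HR 1.25; 80% power; 5% significance level; 528 patients, 587 after 10% dropout. Assumptions made here: exponential PFS, periods are months, and every questionnaire that is due is completed. A hazard of 0.12 implies a median of ln 2/0.12 = 5.8 months, not 8. That mismatch is a separate matter, so both values serve as a range.

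**The plan's own figure.** The event probability is 1 - [exp(-0.12 × 12) - exp(-0.12 × 48)]/(0.12 × 36) = 0.946. With one-sided 5%, Schoenfeld's formula gives 497 events, or 497/0.946 = 525 patients; Freedman's gives 501 events, or 530 patients. Both agree with 528. Then 528/0.90 = 587. The sample size reproduces and is not affected by this point.

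**Share still due a questionnaire under the footnote**, exp(-h t):

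| Month | h = 0.12 | h = ln 2/8 = 0.0866 |
|---|---|---|
| 1 | 88.7% | 91.7% |
| 3 | 69.8% | 77.1% |
| 6 | 48.7% (286 of 587) | 59.5% (349) |
| 9 | 34.0% (199) | 45.9% (269) |
| 12 | 23.7% (139) | 35.4% (208) |

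The complements are 41-51% progressed or dead at 6 months and 65-76% at 12 months. Under the alive-patients rule the number due at each visit is the number of survivors. The documents give no overall survival figure, so that number, and hence the avoidable loss, cannot be computed.

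**Recording time in year 1**, (1 - exp(-12h))/h:
- h = 0.12: (1 - 0.237)/0.12 = 6.36 months.
- h = 0.0866: (1 - 0.354)/0.0866 = 7.46 months.

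**Difference between arms if the true HR equals the margin of 1.25:**
- h = 0.12 × 1.25 = 0.15: (1 - 0.165)/0.15 = 5.56 months. Relative to 6.36 months, 1 - 5.56/6.36 is about 12% less recording time. At month 12, 23.7% versus 16.5% would still be followed.
- Starting from median 8 months, h = 0.0866 × 1.25 = 0.1083: (1 - 0.273)/0.1083 = 6.72 months. Relative to 7.46 months this is about 10% less.

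With the same constant admission rate in both arms, recorded admissions fall in proportion to recording time. Part of the shorter time is due to deaths, after which no admission can occur under any rule.

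**The case against.** The strongest reply is that the harm is conditional. The text after Table 1 already plans follow-up of everyone alive, and Outcome measures fixes the admissions window as the first year. Table 1 marks hospitalisations as standard of care, and clinical data are extracted from electronic health records (Data collection, management and monitoring), so later admissions are retrievable. The design assumes HR 1, under which stopping at progression would be balanced between arms. Stopping may also be deliberate, to confine quality of life to first-line treatment and keep the burden low. All of this is fair, and it limits the point to a conflict between rules and what follows from one way of resolving it. It does not remove the conflict: nothing says which rule governs, or that admissions will be looked up after progression. A non-inferiority trial also cannot take HR 1 for granted.

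Two stronger readings are tempting, and the documents do not support them.

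- A reader might infer that quality of life, function, admissions and QALYs are compared only in progression-free patients. Even under the footnote, every patient contributes until progression, with 89-92% still due at month 1. The planned mixed models use all observed visits, although they do not by themselves remove missingness driven by progression. The economic comparison is by intention to treat, and Table 1 follows survival to the end of the study.
- A reader might infer that a first-year cost-effectiveness endpoint contradicts a life-long horizon. Secondary outcomes describes care costs collected to month 12 and then extrapolated by modelling, which is a coherent sequence. Where post-progression model inputs come from is detail that an article may leave to the full protocol. What remains is that, under the footnote, the trial's own questionnaires would supply no post-progression EQ-5D or care data.

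**Conclusion.** The point holds as an inconsistency in the current text with a material consequence if it is resolved the restrictive way. The footnote conflicts with the alive-patients rule, the hospitalisation column conflicts with the first-year endpoint, and the end-of-study sentence leaves the scope of follow-up unclear.

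If the footnote and column govern, 41-51% of patients would be past the stopping point by 6 months and 65-76% by 12 months. It would be wrong to read these as the share of data lost through the footnote: they include deaths and are upper bounds. The between-arm effect on recording time is about 10-12% at HR 1.25 and nil at HR 1. All figures rest on exponential PFS with periods in months, and the admission effect on equal, constant admission rates. The primary endpoint and the sample size are unaffected. The change should be made, because missed questionnaires cannot be recovered later.

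**What to change.** 1. Remove the progression limit from the Table 1 footnote so that it matches the text: all alive patients are invited at 1, 3, 6, 9 and 12 months, whatever their progression or treatment status.
2. Record unplanned admissions from health records to 12 months for every randomised patient, and mark this in the Hospitalisations row of Table 1.
3. In Treatment monitoring, state that the end of the study at progression or first-line discontinuation refers to study treatment and not to follow-up. This concerns data collection only and changes no treatment rule.

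**Cost.** Some extra telephone or email questionnaires and chart review for patients alive after progression. No additional visits are needed and the sample size does not change. The questionnaires are an added burden for patients who may be unwell, but the text after Table 1 already plans them.

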### Outcome measures

The *primary outcome* of the study is PFS, defined as time from randomisation until either radiological or clinical progression or death due to any cause, whichever occurs first. Timepoints of measurements are presented in table 1. In case of clinical progression as judged by the local principal investigator, local investigators should explain the base of clinical progression. *Secondary endpoints* include QoL (measured by the EQ-5D and EORTC Core QLQ-C30 questionnaires after 1, 3, 6, 9 and 12 months), physical functioning (measured with the Katz ADL, the Lawton IADL and home and informal care after 1, 3, 6, 9 and 12 months), grade≥3 chemotherapy-related toxicity according to the CTCAE during study treatment, dose reductions during study treatment, number of treatment cycles, unplanned hospital admissions within the first year, OS, cumulative received dose and cost-effectiveness in the first year. Predictive geriatric markers of poor outcomes will be identified using the baseline GA.

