The Geriatric 8 (G8) Questionnaire is a geriatric screening tool that detects health deficits in different domains and risk of frailty in older patients.^12^ The tool has been well validated in oncology practice, with various studies demonstrating that older adults who score low on the G8 were more likely to experience chemotherapy-related toxicity compared with those with a normal G8 Score.^7 8 13^ The G8 serves as a simple and easy-to-use risk stratification tool for toxicity, offering a practical alternative to the geriatric assessment (GA), which is much more time-consuming and ideally should be done by trained staff. Additionally, the G8 tool is already widely used in Dutch hospitals, as underscored by a recent study showing that 97% of Dutch hospitals offering colorectal cancer surgery use the G8 for frailty screening,^14^ which will facilitate its implementation. Therefore, the G8 can be used for a tailor-made treatment decision between monotherapy or doublet chemotherapy.

Another potential solution to reduce toxicity risk is to perform upfront dose reduction of chemotherapy. Prior studies demonstrated that upfront dose reduction of chemotherapy in older adults with advanced cancer decreased toxicity rates by 20%–30%, while maintaining efficacy.^15 16^ For example, the phase II NORDIC9 trial compared full-dose S1 monotherapy with upfront dose-reduced S1 with oxaliplatin in 160 older adults with metastatic colorectal cancer judged ‘unfit’ for full-dose treatment by their oncologist.^16^ The study showed that doublet chemotherapy with upfront dose reduction resulted in a better progression-free survival (PFS) (6 months for reduced dosed vs 5 months for full dose), with markedly reduced toxicity rates in the dose-reduced arm (43% vs 62%, respectively). In addition, the GO2 trial compared different levels of dose-reduced capecitabine plus oxaliplatin (CAPOX) in 559 advanced gastro-oesophageal cancer patients deemed unfit for full-dose chemotherapy. Results showed that upfront dose-reduced chemotherapy was non-inferior to full-dose treatment and resulted in an improved toxicity profile, even in less frail patients.^17^ Thus, dose-reduced chemotherapy can improve QoL and physical functioning and decrease hospital admissions. Despite these promising results, upfront dose reduction is not yet widely adopted in Dutch daily practice and has not yet been studied in a phase III study or in chemotherapy schemes used in the Dutch setting.

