### Study objectives

The primary objective of the DOSAGE study is to show that upfront dose-reduced chemotherapy in patients with metastatic colorectal cancer is non-inferior to full-dose treatment in terms of PFS with adaption of the treatment plan (monotherapy or doublet chemotherapy) based on expected risk of treatment toxicity for the individual patient. Secondary objectives are to investigate that upfront dose-reduced chemotherapy will lead to lower toxicity rates, better QoL and physical functioning, less dose reductions, treatment withdrawals and hospital admissions, a better overall survival (OS), a higher cumulative received dose and lower healthcare costs.

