## Methods

### Study design

The DOSAGE study is an investigator-initiated, phase III, open-label, non-inferiority, randomised controlled clinical trial. The trial will enrol patients in 36 Dutch hospitals (2 academic and 34 peripheral hospitals). A list of all participating hospitals can be found at clinicaltrials.gov (NCT06275958).

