### Doublet chemotherapy

Patients classified as low risk will be randomised between doublet chemotherapy with a fluoropyrimidine (physicians’ choice fluorouracil (5-FU) or capecitabine) and oxaliplatin in either full-dose, or with an upfront dose reduction. In the full-dose arm, the following dosing schemes are allowed:

CAPOX: capecitabine 1000 mg/m^2^ at day 1–14 (every 3 weeks) and oxaliplatin 130 mg/m^2^ at day 1 (every 3 weeks).FOLFOX6: 5-FU 400 mg/m^2^ intravenous bolus at day 1 followed by 2400 mg/m^2^ in 46 hours (every 2 weeks), leucovorin 400 mg/m^2^ day 1 (every 2 weeks) and oxaliplatin 85 mg/m^2^ day 1 (every 2 weeks).

In the dose-reduced arm, patients receive an upfront 25% reduction (75% of full dose).

Addition of targeted treatment (bevacizumab or epidermal growth factor receptor (GFR) inhibition) is allowed. Patients with a moderate renal impairment (GFR 30–50 mL/min) will receive a 25% reduced starting dose of capecitabine in the full-dose arm and a 40% reduced starting dose in the dose-reduced arm.

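### The toxicity endpoint counts only events judged chemotherapy-related in an open-label trial, so attribution may bias the comparison towards the reduced dose; an any-cause count should stand beside it

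*Protocol article*

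**What the plan says.** The restriction to chemotherapy-related events appears at three levels of the protocol article.

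- **Endpoint** (Outcome measures): "grade≥3 chemotherapy-related toxicity according to the CTCAE during study treatment", listed as one of several secondary endpoints.
- **Collection** (Treatment monitoring): tolerability is assessed after each cycle as "chemotherapy-related toxicity according to the Common Terminology Criteria for Adverse Events (CTCAE) V.5.0".
- **Analysis** (Secondary outcomes): "A logistic regression model will be estimated to study the effect of groups on chemotherapy-related toxicity".

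The abstract lists the endpoint as grade≥3 toxicity, without the restriction. Table 1 has a row for toxicity before and after every cycle, also without it.

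On blinding, Study design says "The DOSAGE study is an investigator-initiated, phase III, open-label, non-inferiority, randomised controlled clinical trial". On the hypothesis, Study objectives says "Secondary objectives are to investigate that upfront dose-reduced chemotherapy will lead to lower toxicity rates" and gives no size. The article does not say who judges relatedness or by what rule, and it mentions no any-cause comparison.

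**The concern.** A related-only endpoint has two parts: whether a grade≥3 event happened, and whether someone blamed chemotherapy for it. The second part is open to knowledge of the allocation. Patients are 70 or older, and the Introduction describes multimorbidity and physical or cognitive impairment in this population, so another cause is often available. Targeted agents supply a further one: "Addition of targeted treatment (bevacizumab or epidermal growth factor receptor (GFR) inhibition) is allowed". The same event may be blamed on chemotherapy more readily at full dose than at 75%.

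The likely direction of error is the direction of the hypothesis. Lower toxicity is a main reason given for studying dose reduction, so a difference that came partly from labelling would be read as support for the strategy. A lower attributed share in the reduced arm is also what a real benefit would look like, so the related-only count cannot separate the two. A real benefit should lower the any-cause rate, whereas relabelling leaves it unchanged.

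**Working it through.** **Plan's own figure.** There is none to reproduce: the article gives no expected toxicity rate, effect size or power for toxicity. The only planning figure used here is 264 patients per arm (Statistics: sample size and power calculations).

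**Assumed inputs.** The any-cause grade≥3 rate *p* is the same in both arms. The attributed share *a* is the proportion of patients with a grade≥3 event who have one judged chemotherapy-related. The article gives neither, so ranges are shown.

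**Formulas.**
- Recorded rate = *p* × *a*.
- Odds ratio (OR) = [r₂/(1−r₂)] / [r₁/(1−r₁)], with r₁ the recorded rate at full dose and r₂ at reduced dose.
- Chance of two-sided p<0.05 favouring the reduced dose ≈ Φ[(d − 1.96·SE₀)/SE₁]. Here d = r₁ − r₂, SE₀ is the pooled and SE₁ the unpooled standard error, with 264 per arm. Without bias this chance is 2.5%, half of the two-sided 5%.

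**Worked case.** With *p* = 0.60, the full-dose rate is 0.60 × 0.90 = 0.54 and the reduced-dose rate is 0.60 × 0.80 = 0.48. OR = (0.48/0.52)/(0.54/0.46) = 0.79.

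| Any-cause rate, both arms | Attributed, full v reduced | Recorded, full v reduced | OR | Chance of p<0.05 |
|---|---|---|---|---|
| 60% | 90% v 85% | 54% v 51% | 0.89 | 10% |
| 60% | 90% v 80% | 54% v 48% | 0.79 | 28% |
| 60% | 90% v 75% | 54% v 45% | 0.70 | 54% |
| 70% | 90% v 80% | 63% v 56% | 0.75 | 37% |

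The true difference is zero in every row.

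**Range.** Let the any-cause rate run from 50% to 69%, with 90% attributed at full dose.

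| Attributed at reduced dose | Spurious difference, points | Chance of p<0.05 |
|---|---|---|
| 85% | 2.5-3.5 | 8-13% |
| 80% | 5-7 | 21-36% |
| 75% | 7.5-10 | 42-67% |
| 70% | 10-14 | 65-89% |

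**How large a gap would imitate earlier results?** The Introduction cites a phase II trial with toxicity of 62% at full dose and 43% at reduced dose. With 90% attributed at full dose, the common any-cause rate would be 0.62/0.90 = 0.69. The reduced-dose share would have to be 0.90 × 43/62 = 0.62, a gap of about 28 points. The Introduction also says earlier studies "decreased toxicity rates by 20%–30%, while maintaining efficacy". If that is read as a relative decrease, the reduced-dose share would have to be 0.90 × 0.80 = 72% or 0.90 × 0.70 = 63%.

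**The case against.** The strongest reply is that related-only toxicity matches the stated aim, which is to reduce harm from chemotherapy. An any-cause count admits progression and comorbidity events and so dilutes the contrast. Grading and reporting would still be unblinded, so an any-cause count is not free of judgement either. This stands, and it is why the any-cause comparison belongs beside the related-only one and need not replace it.

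A second reply is that a journal article condenses the full protocol, which may already hold causality rules and any-cause recording. That stands for data collection. It does not dispose of the point, because the article states the restriction for the endpoint, the assessment and the model.

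A third reply is that other outcomes offer protection. Unplanned admissions and overall survival need no causal attribution, quality of life and functioning come from questionnaires, and laboratory tests each cycle give some events an objective grade. Targeted therapy is a stratification factor, so its use should be balanced and matters only if its events are attributed differently by arm. These are partial safeguards; none of them measures grade≥3 toxicity.

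Several stronger inferences are not supported:

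- **That attribution by itself would create the whole expected benefit.** The protocol sets no expected size. The 62% v 43% comes from a trial of full-dose S-1 alone against reduced-dose S-1 plus oxaliplatin, a different contrast, and matching it needs a very large attribution gap.
- **That this is the key safety endpoint, or the basis of the PFS margin.** It is one of several secondary endpoints. The margin is justified by previous trials and by consultation with investigators and the patient foundation.
- **That unblinded clinicians are known to make the judgement.** This is a reasonable inference from an open-label trial with data taken from local records, but the article does not name the assessor.

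**Conclusion.** The concern holds in a limited form. A related-only toxicity endpoint in an open-label trial with a one-directional hypothesis is a stated choice, and it leaves the comparison open to attribution that differs by arm. The likely effect is to bias or exaggerate a difference in favour of the reduced dose.

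The size cannot be known from the document. An attribution gap of 5 points gives an artefact of about 3 points, and a gap of 10 points gives 5-7 points. Larger gaps would often yield a nominally significant result with no true difference. These figures rest on assumed any-cause rates of 50-70%, an assumed 90% attributed at full dose, and an unadjusted comparison of two proportions at 264 per arm. The planned covariate-adjusted logistic model would behave somewhat differently. The primary PFS analysis is not affected.

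**What to change.** 1. At the per-cycle toxicity assessments already in Table 1, record every grade≥3 adverse event regardless of cause, if the full protocol does not already require this. Keep the relatedness judgement as a separate field.
2. Prespecify a comparison of any-cause grade≥3 events by randomised arm, reported alongside the chemotherapy-related one. Claim a toxicity benefit only if the two agree in direction and are broadly similar in size.
3. Align the abstract's description of the endpoint with the definition under Outcome measures.

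The cost is a few more form entries and a short addition to the endpoint and analysis text. The any-cause count will carry some dilution from disease- and comorbidity-related events, so a somewhat smaller any-cause difference is to be expected even where the benefit is real. The change should be made early, because events never recorded would be hard to recover. Treatment and visit schedules are unaffected.
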